## Abstract

**Background:**

Actinic keratosis (AK) is characterized by preinvasive, cancerous lesions on sun-exposed skin that negatively affect patient quality of life and may progress to invasive squamous cell carcinoma (SCC). If untreated, AK may either regress or progress to SCC, with significant morbidity and possible lethal outcomes. The most commonly used treatments for AK are cryotherapy, topical chemotherapy and, more recently, photodynamic therapy (PDT). This clinical study is part of a project that aims to create specific light-emitting fabrics (LEFs) that strongly improve the efficiency and reliability of PDT as a treatment for AK.

**Objective:**

This study aims to compare the efficacy and tolerability of a new PDT protocol involving the Flexitheralight device (N-PDT) with the classical protocol involving the Aktilite CL 128 device (C-PDT; Galderma Laboratories) for the treatment of AK. All participants receive both protocols. The primary objective of this study is to compare the lesion response rate after 3 months of N-PDT with C-PDT. Secondary objectives are evaluations of pain and local tolerance during treatment, clinical evolution of the subject's skin, and evaluations of patient quality of life and satisfaction.

**Methods:**

The study is a split-face, intraindividual comparison of two PDT protocols. The total number of patients recruited was 42. Patients were exposed to a continuous red light with the Aktilite CL 128 device on one side of the face and to fractionated red illumination with the new device, Flexitheralight, on the other side of the face. Males or females over the age of 18 years with a clinical diagnosis of at least 10 previously untreated, nonpigmented, nonhyperkeratotic grade I and II AK lesions of the forehead and/or scalp were included and were recruited from the Department of Dermatology of the Centre Hospitalier Universitaire de Lille. The patients came to the investigational center for one treatment session (day 1), and they were followed up after 7 days, 3 months and 6 months. A second treatment session was performed on day 111 in cases in which an incomplete response was observed at the 3-month follow-up. Data will be analyzed using SAS software version 9.4 (SAS Institute Inc). Continuous variables will be reported as means and standard deviations, and categorical variables will be reported as frequencies and percentages. The Shapiro-Wilk test will be used to assess the normality of the distribution.

**Results:**

The clinical investigation was performed by July 2018. Data analysis was performed at the end of 2018, and results are expected to be published in early 2019.

**Conclusions:**

This phase II clinical trial aims to evaluate the noninferior efficacy and superior tolerability of N-PDT compared to that of C-PDT. If N-PDT is both efficacious and tolerable, N-PDT could become the treatment of choice for AK due to its ease of implementation in hospitals.

**Trial Registration:**

ClinicalTrials.gov NCT03076918; https://clinicaltrials.gov/ct2/show/NCT03076918 (archived by WebCite at http://www.webcitation.org/771KA0SSK)

**International Registered Report Identifier (IRRID):**

DERR1-10.2196/11530

## Introduction

Actinic keratosis (AK) is characterized by common, preinvasive, cancerous lesions in sun-exposed skin [1-4] that negatively affect the quality of life in patients and may progress to invasive squamous cell carcinoma (SCC) [5]. AK usually develops on areas that are frequently exposed to the sun (eg, face, ears, scalp, neck, forearms, backs of hands). Patients with AK often express embarrassment, worry, and irritation related to the change in appearance of their skin and the unsightly nature of the lesions [6]. In addition causing emotional strain, AK lesions can be painful and easily traumatized, causing bleeding [5,7-9]. If untreated, AK may either regress or progress to SCC, with significant morbidity and possible lethal outcomes [10]. The malignant potential and impossibility of predicting which AK lesions will evolve into SCC have led to the common consensus that AK lesions must be treated [11]. The most commonly used treatments for AK are cryotherapy, topical chemotherapy, and, more recently, photodynamic therapy (PDT) [2,12-16].

PDT is based on the activation of light-sensitive molecules (photosensitizers) that are preferentially localized in the diseased tissues, resulting in the formation of reactive oxygen species and subsequently tissue injury and cell death; 5-aminolevulinic (ALA) and its ester, methyl aminolevulinate (MAL), are both photosensitizer precursors that are most often used for topical PDT. After being topically applied to the skin, these photosensitizer precursors are endogenously converted by the heme biosynthetic pathway into the photosensitizer protoporphyrin IX (PpIX) and other intermediate photosensitizing porphyrins [17]. As abnormal cells accumulate substantially higher levels of PpIX than normal cells [18], the subsequent illumination leads to their selective destruction. PDT with MAL has been shown to be an attractive treatment modality for AK because it enables the treatment of large areas with a high response rate and an excellent cosmetic outcome [19-22].

Classical PDT (C-PDT) is already used, but it involves rigid, planar light source devices (like Aktilite C128, Galderma Laboratories) that do not allow the homogeneous illumination of convex surfaces such as the scalp. Therefore, the dermatologist does not know the actual light dose that is delivered during C-PDT, and some lesions may be undertreated. This limitation could explain some treatment failures [23]. Moreover, C-PDT is only available in specialized environments (hospitals and clinics) and has not been sufficiently developed and widely used.

This clinical study is part of a project that aims to create specific light-emitting fabrics (LEFs) that improve the efficiency and reliability of PDT [24] as a treatment for AK. Flexitheralight is a new device for PDT treatment (N-PDT; U1189, Inserm) that appears to be perfectly adapted for treating skin zones because of its homogeneity, low weight, flexibility, optimal conformability, and low cost. Moreover, the Flexitheralight device can be used at home, following the diagnosis and treatment definition by specialists.

## Methods

### Trial Design

The trial was a proof-of-concept study and was a comparative (split-face and intraindividual comparison), randomized, open-label, single-center evaluation of the noninferiority of N-PDT compared with C-PDT.

### Setting

The study was conducted at the Lille University Hospital in the Department of Dermatology over a period of 24 months until the end of 2017. Forty-two patients were included and were followed for 6 months.

### Device

Flexitheralight is a new illumination device consisting of LEFs connected to a laser source (Figure 1). For fractionated illumination, 3 juxtaposed LEFs, each 20 cm x 5 cm, are positioned on the patient’s head.

Each LEF is connected to a 635 nm laser source, which is tuned to deliver an irradiance of 12.3 mW/cm^2^. This irradiance is controlled by a PD300 photodiode sensor connected to a StarBright laser power meter (both Ophir Optronics Solutions Ltd).

The 3 LEFs are activated sequentially as follows (Figure 2): on for 60 seconds and off for 120 seconds, with the sequence being repeated 50 times. When using these parameters, the total fluence is 37 J/cm^2^ for an illumination time of 2 hours and 30 minutes.

**Figure 1 figure1:**
[figure not shown]
Flexitheralight device.

**Figure 2 figure2:**
[figure not shown]
Fractionated illumination with LEF.

### Participants

To be eligible for the study, patients had to fulfill all the inclusion criteria described in Textbox 1 below. If they had only one of the noninclusion criteria, they were excluded from the study.

Information about the trial was provided to the patients, both orally and in a written format. Written informed consent was obtained from patients at the screening visit before entering the study.

The tolerability of the device was assessed on the first five patients. The study would have been completely interrupted if at least one patient had pain rated at 5 or higher out of 10 in the N-PDT area as measured by the pain assessment scale or at least one serious adverse event related to N-PDT occurred.

Selection criteria.Inclusion criteria:Males or females over the age of 18 yearsClinical diagnosis of at least 10 previously untreated, nonpigmented, nonhyperkeratotic, grade I and II actinic keratosis (AK) lesions of the forehead and/or scalp (according to Olsen et al [25])Other therapies are not unacceptable or considered medically less appropriateSymmetrical repartition of AK in terms of number and severity of lesions on both areas of the forehead and/or scalp. The axis of symmetry between the two areas is defined by the investigator according to the distribution of lesionsAK is diagnosed upon a clinical evaluation (ie, visual inspection and palpation) performed by the investigatorNo treatment of AK received in the previous 30 daysThe two areas to be treated should not be coalescing. A minimum distance of 10 mm between the lesions located on the 2 symmetrical areas is required. A minimum distance of 2 mm between the lesions on the same area is requiredA minimum of 5 lesions and a maximum of 7 lesions with similar dimensions at both symmetrical areas are included. If the number of lesions is more than 7, only 7 lesions in each area are consideredNoninclusion criteria:Patients with porphyriaPatients who are immunosuppressed for idiopathic, disease-specific, or therapeutic reasonsUse of topical corticosteroids on the lesioned areas within 2 weeks before photodynamic therapy (PDT)Patients receiving local treatment (including cryotherapy, curettage-electrocoagulation, or any PDT treatment) of the face/scalp area within the last 30 daysPatients receiving topical treatment (including imiquimod, fluorouracil, diclofenac, or ingenol mebutate) of the face/scalp area within the last 3 monthsUse of topical retinoids, alpha hydroxy acids, urea, or systemic retinoids or chemotherapy or immunotherapy within the 4 last weeksPigmented AK lesionsKnown allergy to ester methyl aminolevulinate or similar PDT compound or excipients of the cream including arachis, peanut, or soya oilParticipation in other clinical studies either currently or within the last 30 daysFemale subjects must meet one of the following criteria:Nonchildbearing potential: postmenopausal or have a confirmed clinical history of sterility (eg, the subject does not have an uterus)Childbearing potential: confirmed negative urine pregnancy test or blood analysis prior to study treatment to exclude pregnancyAny condition that may be associated with a risk of poor protocol compliancePatients currently receiving regular ultraviolet radiation therapy

### Study Objectives and Outcomes

The primary objective is the comparison of the lesion response rate 3 months after either N-PDT or C-PDT. Key secondary objectives are treatment tolerability, complete response rate after 6 months, cosmetic results, patient quality of life, and satisfaction (Table 1).

### Sample Size

The study is designed to have a statistical power of 80% with a one-sided alpha level of .025 to determine noninferiority in terms of a complete lesion response rate 3 months after N-PDT compared with C-PDT. Assuming a complete lesion response rate of 75% in both areas, an intrapatient correlation in both lesions and areas, and a noninferiority margin of 10%, the number of required lesions per area is 245. This value corresponds to 42 patients, assuming 12 lesions per patient (6 lesions per patient per area).

### Allocation and Randomization

Patients who met all of the eligibility criteria were included in the study by central randomization. The randomization schedule was generated by a statistician using the PROC PLAN procedure in SAS statistical software (SAS Institute Inc) with a 1:1 allocation ratio and a block size of 6. The allocation was concealed using sequentially numbered, opaque, sealed envelopes that were opened sequentially by the investigator at the beginning of the treatment.

### Implementation and Blinding

The study was not blinded, and patients and investigators knew the procedure allocation. Efficacy and tolerability were evaluated by investigators who knew the type of treatment assigned to each area. Data will also be analyzed without blinding.

**Table 1 table1:** Criteria for objectives evaluation.

Outcome and description		Visit				
		1^a^	2^b^	3^c^	3bis^d^	4^e^
**Complete response rate**						
	Total disappearance of each lesion			x		x
	Number of patients presenting a 75% lesion reduction rate			x		x
**Tolerability**						
	Evaluation of pain (visual analogic scale)	x			x	
	Local tolerance (adverse event, serious adverse event, concomitant treatments)	x	x		x	
**Cosmetic results**						
	Clinical assessment of the subject’s skin aspect (excellent, good, fair, or poor)	x		x		x
**Quality of life and satisfaction**						
	DLQI^f^ and satisfaction questionnaire	x	x	x	x	x

^a^Visit 1: day 1.

^b^Visit 2: day 7.

^c^Visit 3: at 3 months.

^d^Visit 3bis: day 111.

^e^Visit 4: at 6 months.

^f^DLQI: Dermatology Life Quality Index.

**Figure 3 figure3:**
[figure not shown]
Schematic of the study procedure. V: visit.

### Interventions

As shown in Figure 3, after screening, patients who met all the inclusion criteria and none of the exclusion criteria were randomized and invited to come to the investigation site for 4 visits: day 1, day 7, month 3, and month 6. If an incomplete clinical response was observed at month 3, patients were retreated with PDT during visit 3bis on day 111.

#### Initial Visit: Preparation and Treatment of Lesions

##### Selection of Treatment Areas

Each subject’s skin aspect was evaluated, and the two areas were treated according to the study protocol and randomization design. Randomization was performed after the definition of the axis of symmetry to avoid selection errors (Figure 4).

The global area of the scalp and front of the face was divided into two symmetrical areas (area A and area B) containing the same number and same grades of AK lesions. The areas to be treated were localized between the eyebrows and the neck. Included AK lesions were located, counted, graded, and photographed.

For each patient, *n* lesions in area A were treated with one technique (N-PDT or C-PDT) and *n* lesions in area B were treated with the other technique (C-PDT or N-PDT) (5≤*n*≤7).

**Figure 4 figure4:**
[figure not shown]
Schematic of the randomization process for area A and area B. C-PDT: Aktilite CL 128 device; N-PDT: Flexitheralight device.

Before applying MAL, the areas were prepared by removing the crusts with a small curette and gently scraping the surface of the lesions to roughen the surface.

Pain in the two treated areas was scored by the patient after treatment: first for the N-PDT area and then for the C-PDT area.

Patients complete a quality of life questionnaire (Dermatology Life Quality Index [DLQI]) and a satisfaction questionnaire at the end of the procedure.

The total duration of the treatment procedure (treatment of areas A and B) was approximately 3 hours and 20 minutes.

##### Area A: Classical Photodynamic Therapy

MAL was applied (approximately 1 mm thick) with a spatula on the selected lesions and over an area of 5 to 10 mm of normal skin surrounding the lesions. The treated area was covered with an occlusive (Tegaderm, 3M) and light-proof (aluminium foil) dressing for 3 hours. Afterward, the dressing was removed, the area was cleaned with a saline solution, and the skin was then immediately exposed to a continuous red light spectrum delivered by an Aktilite CL 128 device (Galderma Laboratories) (570 to 670 nm) for 10 minutes for a total light dose of 37 J/cm^2^ (Figure 5).

##### Area B: New Photodynamic Therapy

MAL was applied as described for the area A treatment, and the area was covered with an occlusive and transparent dressing (Tegaderm, 3M) for 30 minutes whereas both a transparent occlusive dressing and a light-proof dressing (aluminium foil) was applied over the area randomized to receive C-PDT. Afterward, the dressing was retained, and irradiation was applied with the Flexitheralight device (635 nm) for 2 hours and 30 minutes. A total light dose of 37 J/cm^2^ was administered (Figure 6). After the end of the illumination, area B was protected with aluminium foil.

#### Follow-Up and Retreatment Visits

Visit 2 occurred 7 days after treatment to evaluate the tolerability and adverse effects of the treatments. Patients completed the DLQI and satisfaction questionnaires. Photographs of the treated areas were captured under standardized conditions.

Visit 3 occurred 3 months after treatment. The investigator evaluated the response to treatment by comparing the lesions between the current visit and the first visit (by referring to paper tracings and photographs taken during the first visit). If some of the treated AK lesions remained, a new visit was scheduled within 3 weeks to treat the remaining lesions. The remaining lesions in each area were located, counted, and graded. Only the presence of lesions was considered and not any changes in their sizes. If a new lesion appeared, it was treated (by the same procedure), but it was not considered for the comparison of lesions between months 3 and 6. Photographs of the two treated areas were taken. Patients completed the DLQI and the satisfaction questionnaires, and all adverse events and concomitant medications were recorded. Patients for whom the AK lesions had completely disappeared were invited to participate in an assessment visit at month 6.

Visit 3bis was optional and scheduled only in cases where at least one AK lesion remained after the first treatment session and only if the investigator considered it necessary for the subject to be treated again with PDT. The same treatment was applied as in visit 1.

Visit 4 occurred 6 months after the initial treatment. The investigator evaluated the treatment response by comparing the lesions between the current visit and the first visit. Photographs of the two treated areas were taken. Patients completed the DLQI and the satisfaction questionnaires, and all adverse events and concomitant medications were recorded.

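### The 6-month complete response comparison measures clearance after up to two sessions, the second at an unblinded investigator's discretion, so it does not show one-session efficacy or its durability

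*Protocol article*

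**What the plan says.** Study Objectives and Outcomes lists "complete response rate after 6 months" among the key secondary objectives. Table 1 places both total lesion disappearance and the 75% reduction criterion at visit 4. Follow-Up and Retreatment Visits has the visit 4 response judged against visit 1. Analysis of Secondary Objectives compares the 75% criterion and the other qualitative outcomes between N-PDT and C-PDT with a generalized linear mixed model.

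A second session could fall between month 3 and month 6. The article describes its trigger in different ways:

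- Abstract, Methods: "A second treatment session was performed on day 111 in cases in which an incomplete response was observed at the 3-month follow-up".
- Interventions: "If an incomplete clinical response was observed at month 3, patients were retreated with PDT during visit 3bis on day 111".
- Follow-Up and Retreatment Visits, under visit 3: "a new visit was scheduled within 3 weeks to treat the remaining lesions".
- The same section, under visit 3bis: the visit was optional, needed at least one remaining lesion, and took place "only if the investigator considered it necessary for the subject to be treated again with PDT".

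The technique did not change at retreatment: "The same treatment was applied as in visit 1". Implementation and Blinding adds: "Efficacy and tolerability were evaluated by investigators who knew the type of treatment assigned to each area".

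**The concern.** Under the stated comparison, a lesion that failed at month 3, was treated again and then cleared counts at 6 months in the same way as a lesion cleared by one session and still clear. The second session depends on the month-3 result, which is itself an outcome of the first session. On the discretionary wording it also depends on the judgement of someone who knows which technique each area received. Retreated lesions are then assessed much sooner after their last session than the others.

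At stake is how the 6-month result is read. Similar rates could be taken as equal lasting effect of one session when part of the clearance came from a second. A difference could partly reflect who was retreated. The three accounts of the trigger also leave open whether retreatment followed a rule or a choice, and the reader needs that to judge the risk of bias.

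**Working it through.** The article gives no figure for the 6-month comparison, so there is none to reproduce. Its sample size concerns month 3 only.

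**Inputs from the article:** 75% complete lesion response in both areas and 6 lesions per area, 12 per patient (Sample Size); second session on day 111; visit 4 at 6 months.

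**Assumptions, not in the article:** month-3 rates of 75% for C-PDT and 65% for N-PDT, as illustration; q, the share of remaining lesions retreated, from 0 to 1; r, clearance after a second session, from 0.30 to 0.80. Steps 3 and 4 also assume no recurrence and no clearance without retreatment.

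**1. Follow-up after the last session.** Six months is about day 180 to 183. 180 − 111 = 69 and 183 − 111 = 72, so retreated lesions are seen after about 70 days. Lesions treated once are seen after 6 months.

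**2. How many patients could be retreated.** At 75% clearance and 12 independent lesions, P(at least one remaining) = 1 − 0.75^12 = 97%. With an intrapatient correlation of 0.10, 0.17 or 0.30 (beta-binomial) it is 89%, 83% or 72%. The article gives no correlation. A single common value of about 0.168 would yield its 245 lesions per area: 2 × 0.75 × 0.25 × (1.960 + 0.842)² / 0.10² = 294.3, and 294.3 × (1 − 0.168) = 245. Most patients would be candidates on any of these values.

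**3. Similar retreatment in both areas.** Month-6 rate = p3 + (1 − p3)·q·r, with p3 the month-3 rate. If q and r are equal, D6 = D3 × (1 − q·r), where D = N-PDT − C-PDT.

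| q | r | C-PDT | N-PDT | D6 (points) |
|---|---|---|---|---|
| 1 | 0.4 | 85% | 79% | −6 |
| 1 | 0.6 | 90% | 86% | −4 |
| 1 | 0.8 | 95% | 93% | −2 |
| 0.5 | 0.5 | 81.25% | 73.75% | −7.5 |

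**4. Retreatment or its success differs by technique.**

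| Month 3, C / N | q, C / N | r, C / N | C-PDT | N-PDT | D6 (points) |
|---|---|---|---|---|---|
| 75 / 65 | 1 / 0.5 | 0.75 / 0.75 | 93.75% | 78.1% | −15.6 |
| 75 / 65 | 0.5 / 1 | 0.75 / 0.75 | 84.4% | 91.25% | +6.9 |
| 75 / 65 | 1 / 1 | 0.75 / 0.50 | 93.75% | 82.5% | −11.25 |
| 75 / 65 | 1 / 1 | 0.75 / 0.30 | 93.75% | 75.5% | −18.25 |
| 75 / 65 | 1 / 1 | 0.75 / 0.65 | 93.75% | 87.75% | −6 |
| 75 / 75 | 1 / 0.5 | 0.75 / 0.75 | 93.75% | 84.4% | −9.4 |

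Swapping the retreatment shares in the last row gives +9.4 points.

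**5. Durability.** Suppose 75% are clear at month 3, 25% of those recur, and every remaining lesion is retreated with r = 0.75. The month-6 rate is 0.75 × 0.75 + 0.25 × 0.75 = 0.5625 + 0.1875 = 75.0%, the same as at month 3. Without retreatment it would be 56.25%. The overall rate hides the recurrence.

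**The case against.** The strongest case against the point is that clearance after up to two sessions is a legitimate outcome of the schedule, that the article never calls the 6-month result durability, and that the handling of retreated lesions may stand in a full protocol or analysis plan that is not shown. All of this stands. The point is therefore not that a rule is missing. It is what the stated comparison measures, and that the article contradicts itself on the retreatment trigger. One can also say that the abstract and Interventions are summaries and that the visit 3bis text gives the full condition. That is plausible, but the visit 3 text in the same section again has the visit simply scheduled.

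Four stronger readings are tempting and are not supported:

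- **Retreatment shrinks any real difference.** A reader might infer this from step 3, but it needs similar q and r in both areas. Similar shares are a reasonable base case, since the decision is described per subject. Unblinded discretion or unequal second-session success can break the condition, as step 4 shows.
- **The weaker technique was used twice as often.** At 75% against 65%, the remaining lesions are 25% against 35%, a ratio of 1.4. For areas of 6 independent lesions with at least one remaining, it is 1 − 0.75^6 = 82% against 1 − 0.65^6 = 92%, a ratio of 1.1. The text also leaves open whether both areas were retreated together.
- **The 6-month result would lend false support to noninferiority.** The margin and the confidence-interval rule apply only at month 3, before any retreatment. No noninferiority conclusion is planned at 6 months.
- **The trial cannot show durability.** Remaining lesions were located and counted by area at month 3, and the article mentions a comparison between months 3 and 6. The limit lies in the overall rate, not in the data.

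**Conclusion.** The concern holds for one key secondary outcome. The overall 6-month rate is clearance after up to two sessions, with about 70 days of follow-up for retreated lesions, and should not be read as one-session efficacy or its durability. Under similar retreatment and similar second-session success, an assumed 10-point month-3 gap falls to between 2 and 6 points for r from 0.8 to 0.4 at q = 1. Under unequal conditions the same gap ran from −18.25 to +6.9 points in the cases shown, and 9.4 points arose from no true difference. These sizes rest on assumed q, r and month-3 rates, so the direction of any bias in this trial is unknown. The month-3 primary endpoint and its noninferiority test are unaffected. The conflict over whether retreatment was automatic or discretionary is in the text and needs no assumption.

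**What to change.** 1. Reconcile the abstract, Interventions, and Follow-Up and Retreatment Visits on whether the day 111 session was automatic or discretionary. This review takes no position on which rule should apply.
2. Label the 6-month response as clearance after up to two sessions.
3. Add a between-arm comparison of sustained one-session clearance: a lesion is a response if clear at month 3 and still clear at month 6, and a lesion present at month 3 is a non-response whether or not it was retreated. Keep all included lesions in the denominator, because the subset clear at month 3 is selected after treatment. Only presence at month 3 should trigger non-response: if a whole area was treated again, a lesion already clear should not be scored as a failure for that. State that a second session could spill over onto lesions already clear.
4. Report the number of lesions and areas retreated per arm.

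The added comparison needs only lesion status at months 3 and 6. The counts in item 4 need the treatment record, since Table 1 lists only tolerability and questionnaires at visit 3bis. The article reports data analysis as already performed, so unless the full plan has this comparison, mark it as added afterwards. The cost is one extra analysis and some wording. The sustained rate cannot exceed the month-3 rate, so it will look less favourable than the present 6-month rate in both arms.
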